### Interventions

The SNEHA center will be a community space in a rented room within the cluster that it serves. Each center will be a base for three salaried community organizers, a teacher to work on early child development, and a helper to provide services for malnourished children. Each community organizer will cover approximately 200 households, a ratio designed to fit with the proposed coverage of the Urban Social Health Activist proposed for the NUHM. Every two centers will be supervised by a program officer, and every six to eight by a program coordinator. Community organizers will communicate with three constituencies - individual residents, collectives and service providers - through five axes of intervention: consultations, home visits, group meetings, community events and communication with service providers (Figure 2). Within an integrated framework, the priority health issues will be maternity care, family planning, childhood nutrition and health, and violence against women and children.

**Figure 2 F2:**
[figure not shown]
**Pathways to impact for the community resource center model.** ICDS, Integrated Child Development Services; IYCF, Infant and Young Child Feeding

### Inception

The community organizers will map their working areas and identify key services and institutions. A series of participatory learning and action exercises (micro-planning) will follow, and will be a first step to involving residents in voluntary activities such as community action groups, parents’ and youth groups, and support for the center. Community organizers will lead visits to local NGOs and service providers in order to establish a referral network, avoid duplication of care, and encourage uptake. The findings of the process will be disseminated in the community and a process of participatory planning and monitoring initiated.

### Home visits

Community organizers will maintain a numbered electronic profile of each family in their catchment areas. They will make approximately six home visits daily and record their activities using electronic data capture on smartphones and a database system in CommCare (www.commcarehq.org). They will identify family health needs in each of the four priority areas, provide relevant information, guide and support family members to take action, and reinforce successful experiences through peer learning at group meetings and community events. Their support options will be information and advice, referral and accompaniment to SNEHA or another organization, or direct service provision. Examples of information include sources of maternity care, danger signs, the *Janani Suraksha Yojana* safe maternity incentive, family planning, infant feeding, immunization, and domestic violence. Examples of advice and action include referral to health providers, accompaniment to support access, arrangement of day care for childhood malnutrition, referral for counseling for violence, and provision of contraception through a partnership with the Family Planning Association of India.

### Group meetings

Community organizers will facilitate daily group meetings, at the center or elsewhere in the community. Meetings will follow a participatory action research cycle addressing issues of concern for pregnant women, new mothers and mothers of young children, adolescents, and local stakeholders.

### Community events

With input from SNEHA programs, community organizers will act as local facilitators for rallies, street drama, competitions, and health campaigns. Community members - especially the youth - will be mobilized and trained to participate in community processes and action.

### Service provision

We will work with the Municipal Corporation, the Integrated Child Development Services (ICDS), local NGOs, the police, and community-based organizations to improve availability, access and uptake of services. Community organizers will mobilize community members to increase uptake of existing services such as immunization and medical camps, and will facilitate interaction meetings for community members and service providers. The resource centers will themselves provide some services: nutritional support, early childhood stimulation, medical consultations, and support for women and children facing violence. Because we are concerned about the refractory nature of childhood malnutrition, we are partnering with the ICDS and Child Rights and You (http://www.cry.org) to implement protocols for identification of malnourished children. A teacher and a helper will support children under 5 years of age with moderate or severe acute malnutrition, through supplementary feeding, provision of ICDS take-home rations, immunization and deworming, and growth monitoring, with home follow-up by resource center workers. Concurrently, we will run early child development activities designed in consultation with Mumbai Mobile Creches. Mothers will be sensitized to the health and development needs of their children and involved in center activities through regular home visits and group meetings. Community organizers will be supported by two medical officers with access to basic medicines, and through outreach pediatric camps organized by the Municipal Corporation. Community organizers will identify domestic violence, and SNEHA counselors will be available for support.

## Outcomes

The outcomes will be assessed through a household census after 2 years of resource center operations. The intervention will address women’s and children’s health in general, including the health of adolescents and unmarried women. We have been more selective in terms of evaluation, since outcomes such as family planning, pregnancies, and deliveries are best addressed in the context by focusing on married women. They also include consultations for domestic violence, which are not limited to married women and will be examined through consultation records rather than cross-sectional data.

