### Secondary outcomes

1. Number of consultations for violence against women or children.

2. Proportion of home deliveries for births in the preceding 1 year.

3. Proportion of pregnancies in the preceding 2 years to women under 19 years under age.

4. Proportion of public sector institutional deliveries for which the *Janani Suraksha Yojana* birth incentive was received.

5. Proportion of children under 5 years of age with height for age less than 2 SD below the median for age and sex.

6. Proportion of children under 5 years of age with weight for age less than 2 SD below the median for age and sex.

7. Proportion of children born in the preceding 2 years who received food supplements, health check-ups, early childhood development intervention, or had their weight measured at ICDS centers.

8. Infant and Young Child Feeding core indicators [17].

a. Early initiation of breastfeeding: proportion of children born in the last 24 months who were put to the breast within 1 hour of birth

a. Exclusive breastfeeding under 6 months: proportion of infants aged <6 months who received only breast milk during the previous day

a. Continued breastfeeding at 1 year: proportion of children aged 12 to 15 months who received breast milk during the previous day

a. Introduction of solid, semi-solid or soft foods: proportion of infants aged 6 to 8 months who received solid, semi-solid or soft foods during the previous day

a. Minimum dietary diversity: proportion of children aged 6 to 23 months who receive foods from four or more food groups

a. Minimum meal frequency: proportion of breastfed and non-breastfed children aged 6 to 23 months who receive solid, semi-solid, or soft foods (but including milk feeds for non-breastfed children) the minimum number of times or more

a. Minimum acceptable diet: proportion of children aged 6 to 23 months who receive a minimum acceptable diet

a. Consumption of iron-rich foods: proportion of children aged 6 to 23 months who receive an iron-rich or iron-fortified food

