### Data collection

Data are collected in baseline and endline censuses of cluster households. Two teams of six interviewers and one program officer cover a cluster at a time, defining its boundaries, mapping it and numbering the households. Each interviewer is allocated 10 households at a time, preferentially interviewing all married women aged 15 to 49 years. If none lives in a household, or if she is absent at three visits, another adult over 18 years of age is interviewed. The interview enumerates household members, their ages, schooling and livelihoods. It then covers duration of residence, assets and amenities, housing fabric, and faith. Women aged 15 to 49 years provide brief maternity histories and information on family planning. If they have been pregnant in the preceding 2 years, they are asked about antenatal care, delivery location and outcomes, and infant feeding. Information on immunizations and use of the ICDS is collected for all children under 5 years of age. Children are listed and their weights and heights are measured on designated days at the end of each cluster census. Data are entered on smartphones running Open Data Kit (ODK: http://opendatakit.org) on the Google Android operating system (http://www.android.com). A program officer will observe 5% of interviews. The interface includes generation of unique identifiers for women aged 15 to 49 years and children under 5 years of age, automatic skips and validation constraints to minimize error.

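### The violence secondary outcome is a count from consultation records, and the only case-finding and service recording described belong to the intervention, so a between-arm comparison would probably mix unequal capture with any real change

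*Protocol article*

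**What the plan says.** The Outcomes section opens with a general rule: "The outcomes will be assessed through a household census after 2 years of resource center operations". It then makes one exception. Consultations for domestic violence, which are not confined to married women, "will be examined through consultation records rather than cross-sectional data". The Secondary outcomes list puts the item first, as "Number of consultations for violence against women or children", with no denominator, period or record owner.

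Other sections describe how such consultations arise:

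- **Interventions:** community organizers work "through five axes of intervention: consultations, home visits, group meetings, community events and communication with service providers". Violence against women and children is one of four priority health issues.
- **Home visits:** organizers look for needs in each priority area, can refer for violence counseling, and "record their activities using electronic data capture on smartphones and a database system in CommCare".
- **Service provision:** the services that the centers themselves offer include "medical consultations, and support for women and children facing violence". The section ends: "Community organizers will identify domestic violence, and SNEHA counselors will be available for support".

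For the trial's own measurement, the Data collection section says "Data are collected in baseline and endline censuses of cluster households". The interview topics that it lists contain no violence item.

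**The concern.** An outcome compared between randomized arms should be ascertained in the same way in each. The census does that for the other outcomes. The violence item is moved to records, and the steps that the article describes as producing such records (finding the case, consulting, counseling, logging) are things the intervention does. Control clusters have no center and no community organizers.

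If the records are mainly program records, the count partly measures how much of the intervention was delivered, and a consultation by a control resident has little or no chance of being counted. A higher count in intervention clusters could then be reported as a secondary effect of the centers when help-seeking had changed less than the count suggests, or not at all.

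**Working it through.** The article gives no expected count, rate, effect size or power for this outcome; Table 1 covers only the primary outcomes. There is no stated figure to reproduce. The check has two parts.

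**1. Who generates the data in each arm, on the text as written**

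| Step | Intervention clusters | Control clusters |
|---|---|---|
| Case-finding | Community organizers, through home visits | None described |
| Consultation and counseling | Resource center and the organization's counselors | None described |
| Recording of service activity | CommCare, kept by organizers | None described |
| Trial data collection | Baseline and endline census | Baseline and endline census |
| Violence item in the listed census content | None | None |

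The one instrument shared by both arms does not carry the outcome. The service recording that is described runs in one arm.

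**2. What unequal capture would do**

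Let the capture share be the proportion of all consultations by a cluster's residents that appear in the records used. Then:

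apparent rate ratio = true rate ratio × (capture share, intervention ÷ capture share, control).

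Inputs: 20 clusters per arm (Trial design). The rest are assumptions, because the document gives no figures: true rate ratio 1; capture 80% in intervention clusters; a mean of 5, 15 or 40 true consultations per cluster; between-cluster coefficient of variation 0.25. Counts were simulated as Poisson with gamma variation between clusters and compared by a t-test on cluster counts at two-sided 0.05, with 3,000 runs per setting.

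| Control capture | Apparent rate ratio | False-positive rate at mean 5 / 15 / 40 |
|---|---|---|
| 80% | 0.80/0.80 = 1.00 | 4.9% / 4.9% / 4.3% |
| 60% | 0.80/0.60 = 1.33 | 32.6% / 59.5% / 79.1% |
| 40% | 0.80/0.40 = 2.00 | 91.0% / 99.9% / 100% |
| 20% | 0.80/0.20 = 4.00 | 100% / 100% / 100% |

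The ratios only restate the assumed shares and do not estimate the bias in this trial. The simulation adds two things. With equal capture the test behaves properly. With moderately unequal capture it often declares a difference that does not exist.

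**The case against.** The strongest objection is that the article never says whose records are meant. Home visits can lead to referral to the organization or to another one, and the counselors are not among the staff listed for each center. Records of a counseling service open to residents of both arms, tagged by area of residence, would fit the same sentence. This stands. A reader might infer that the records are solely those the intervention generates, so that the control count is zero by design. The document does not state that.

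A second objection also stands. The outcome is use of a service, which the centers aim to increase. More consultations in intervention clusters can be a genuine and intended effect. A reader might conclude that any between-arm comparison is biased by construction, but bias arises only if capture differs by arm, or if the count is read as prevalence of violence or as total help-seeking.

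Third, a reader might say that the planned logistic model cannot handle a count. The Analysis plan section states that model for the primary outcomes and refers to a separate sealed plan, which is not shown. A count model, period and denominator could be in it, and their absence from the article is not the point made here.

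The choice of source is different, because the article itself makes it. It takes this outcome out of the shared census and describes service recording only within the intervention. That goes beyond omitted detail.

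**Conclusion.** The point holds in a limited form. As described, a between-arm comparison of violence consultations would probably reflect unequal capture and delivery of the intervention along with any true change in help-seeking. This rests on inference from the steps the article describes, since the record owner is not named. It would fall away if the records were shown to cover residents of both arms alike.

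The size cannot be determined from the document. Under equal true rates and 80% capture in intervention clusters, apparent rate ratios run from 1.0 to 4.0 as control capture falls from 80% to 20%. Severity is moderate: this is one of eight numbered secondary outcomes, no power claim is attached to it, and the three primary outcomes come from the census in both arms.

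**What to change.** The simplest change is to move the item from the secondary outcomes to the process indicators and report it for intervention clusters only, with no between-arm test.

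If a comparison is kept:

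1. Name the record sources, and use only those that cover residents of both arms alike.
2. Assign each consultation to a trial cluster by the client's residence.
3. Analyse a rate per enumerated population with a cluster-level count model. The census already lists household members, so the denominator is available.
4. Interpret the result as service use, not as prevalence of violence.
5. Do not exclude center-initiated consultations. That would remove events from one arm only and could bias the comparison the other way if centers draw people who would have consulted elsewhere.

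The first option changes one line of the outcome list and gives up one comparative secondary claim. The second narrows that claim and requires access to records that identify residence. Neither affects the primary outcomes or the sample size.

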### Primary outcomes

1. Unmet need for family planning in women aged 15 to 49 years: based on the London Measure of Unplanned Pregnancy, a six-question module that has been tested in urban India [15].

2. Proportion of children under 5 years of age not fully immunized for their ages: based on Indian Academy of Pediatrics recommendations [16].

3. Proportion of children under 5 years of age with weight for height less than 2 standard deviations (SD) below the median for age and sex.

### Secondary outcomes

1. Number of consultations for violence against women or children.

2. Proportion of home deliveries for births in the preceding 1 year.

3. Proportion of pregnancies in the preceding 2 years to women under 19 years under age.

4. Proportion of public sector institutional deliveries for which the *Janani Suraksha Yojana* birth incentive was received.

5. Proportion of children under 5 years of age with height for age less than 2 SD below the median for age and sex.

6. Proportion of children under 5 years of age with weight for age less than 2 SD below the median for age and sex.

7. Proportion of children born in the preceding 2 years who received food supplements, health check-ups, early childhood development intervention, or had their weight measured at ICDS centers.

8. Infant and Young Child Feeding core indicators [17].

a. Early initiation of breastfeeding: proportion of children born in the last 24 months who were put to the breast within 1 hour of birth

a. Exclusive breastfeeding under 6 months: proportion of infants aged <6 months who received only breast milk during the previous day

a. Continued breastfeeding at 1 year: proportion of children aged 12 to 15 months who received breast milk during the previous day

a. Introduction of solid, semi-solid or soft foods: proportion of infants aged 6 to 8 months who received solid, semi-solid or soft foods during the previous day

a. Minimum dietary diversity: proportion of children aged 6 to 23 months who receive foods from four or more food groups

a. Minimum meal frequency: proportion of breastfed and non-breastfed children aged 6 to 23 months who receive solid, semi-solid, or soft foods (but including milk feeds for non-breastfed children) the minimum number of times or more

a. Minimum acceptable diet: proportion of children aged 6 to 23 months who receive a minimum acceptable diet

a. Consumption of iron-rich foods: proportion of children aged 6 to 23 months who receive an iron-rich or iron-fortified food

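### Secondary outcome 3 expresses adolescent pregnancy as a share of all pregnancies, a denominator the intervention aims to change, so the share cannot show whether adolescent pregnancy fell

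*Protocol article*

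**What the plan says.** Protocol article, Secondary outcomes, item 3: "Proportion of pregnancies in the preceding 2 years to women under 19 years under age". I read the last words as under 19 years of age. The numerator is adolescent pregnancies and the denominator is every pregnancy in the window. The Abstract describes the topic of this item simply as adolescent pregnancies.

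Three other places bear on the denominator:

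- Interventions: "the priority health issues will be maternity care, family planning, childhood nutrition and health, and violence against women and children".
- Home visits, among the examples of what organizers do: "provision of contraception through a partnership with the Family Planning Association of India".
- Primary outcomes, item 1: "Unmet need for family planning in women aged 15 to 49 years".

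On available data, the Data collection section states: "The interview enumerates household members, their ages, schooling and livelihoods". It adds that women aged 15 to 49 give a short maternity history, with further questions for those pregnant in the last 2 years.

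**The concern.** Contraception is offered across the reproductive ages, and its success is judged by a primary outcome covering those same ages. If it works, the total number of pregnancies in intervention clusters should fall. That total is the denominator of outcome 3, so the outcome responds to what happens in women of 19 and over as well as in adolescents.

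A real reduction in adolescent pregnancy could then appear as no effect, or as an apparent rise, because family planning also succeeded among older women. Conversely, a fall in the share could be read as a benefit to adolescents when only the age mix had moved. The outcome would not answer the question that the Abstract sets for it.

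**Working it through.** The article states no rate, power or sample size for this outcome, so there is no figure of its own to reproduce. The check is ratio arithmetic.

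**Inputs from the article.** 80 pregnancies per cluster in the preceding 2 years (Sample size) and 20 clusters per arm (Trial design): 80 × 20 = 1,600 pregnancies per arm.

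**Assumed inputs, not in the documents.** The adolescent share without intervention (3%, 5% or 10%) and the proportional falls under intervention: *a* for pregnancies under 19, *o* for pregnancies at 19 and over.

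**Formula.** With A adolescent and O older pregnancies before any effect,

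share after = A(1 − a) / [A(1 − a) + O(1 − o)].

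Dividing the odds after by the odds before gives

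odds ratio = (1 − a) / (1 − o).

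The starting share cancels. The direction depends only on whether *a* or *o* is larger.

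**Adolescent fall 10%, older fall 20%** (odds ratio 0.90/0.80 = 1.125):

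| Assumed share | Adolescent pregnancies | Older pregnancies | Share after |
|---|---|---|---|
| 3% | 48 → 43.2 | 1,552 → 1,241.6 | 43.2/1,284.8 = 3.4% |
| 5% | 80 → 72 | 1,520 → 1,216 | 72/1,288 = 5.6% |
| 10% | 160 → 144 | 1,440 → 1,152 | 144/1,296 = 11.1% |

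Adolescent pregnancies fall in every row, and the share rises in every row.

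**Other patterns:**

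- Both fall 20%, starting at 10%: 128/(128 + 1,152) = 10.0%. The odds ratio is 1.00 and a real benefit is invisible.
- No adolescent fall, older fall 15%, starting at 10%: 160/(160 + 1,224) = 11.6%.
- Smaller effects, adolescent 5% and older 10%, starting at 10%: 152/(152 + 1,296) = 10.5%.
- Adolescent fall 20%, older fall 10%, starting at 5%: 64/(64 + 1,368) = 4.5%. Here the share moves the right way.

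**Per-woman measure.** If N women were at risk of an adolescent pregnancy, the rate goes from A/N to A(1 − a)/N, a ratio of 1 − a. A 10% fall in adolescent pregnancies gives a ratio of 0.90 whatever *o* is. This assumes that N is the same in both cases and treats each pregnancy as one woman.

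**The case against.** **The sizes are assumed, and the distortion may be small.** This stands. Nothing in the article supports a 20% fall in older pregnancies, or a fall twice that in adolescents. The nearest planning figure is a detectable change in unmet need from 46% to 41% (Table 1), which is not a fertility effect. Even in the 10.0% to 11.1% illustration, the standard error of the difference before clustering is √(0.1 × 0.9/1,600 + 0.111 × 0.889/1,296) ≈ 1.15 points, about the size of the shift itself. A formal finding of harm is therefore unlikely on those inputs. What does not depend on them is the rule of direction: equal falls show nothing, and a larger older fall reverses the sign.

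**A reader might infer that the comparison loses the protection of randomization.** It does not. Clusters are randomized, and a difference between arms in the cluster-level share is still an effect of allocation. The weakness lies in what that effect means.

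**A reader might extend the point to secondary outcome 4**, "Proportion of public sector institutional deliveries for which the" birth incentive was received, since the centers work "to improve availability, access and uptake of services" and so may alter where women deliver. The documents do not carry this. Receipt among public sector deliveries is a reasonable intended quantity. A misleading fall needs lower receipt among births that move into the public sector. On assumed figures of 50 public deliveries per 100 births with 30% receipt, moving in 10 births with 10% receipt gives (15 + 1)/60 = 26.7%, but with 30% receipt gives (15 + 3)/60 = 30.0%, no change. The article gives no receipt rates and does not say that the public share will rise. The organizers inform women about this incentive and support access to care, so low receipt in moved births cannot be presumed. Movement out of the home is reported separately as "Proportion of home deliveries for births in the preceding 1 year". An all-births denominator has its own fault: in the first example it rises from 15 to 16 per 100 births through relocation alone.

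**A separate analysis plan exists and is not shown.** It might add counts or rates. The denominator of outcome 3 is nevertheless fixed in the article's own outcome list, and the point concerns that definition.

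**Conclusion.** The point holds for secondary outcome 3 as a matter of interpretation. The share mixes a change in adolescent pregnancy with a change at older ages, and the intervention is designed to produce both. On the odds scale it reports (1 − a)/(1 − o) rather than 1 − a.

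Wrong-way movement is possible but not inevitable; it occurs when pregnancies fall proportionally more at 19 and over. The illustrative rises (3.0% to 3.4%, 5.0% to 5.6%, 10.0% to 11.1%) rest entirely on assumed shares and falls. The conclusion that the share cannot identify the adolescent effect rests only on the stated definition and the stated aims of the intervention.

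The documents do not support a claim of lost randomization, a prediction that the outcome will show harm, or a change to outcome 4. The primary outcomes, their analysis and the sample size are unaffected.

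**What to change.** Redefine secondary outcome 3 as follows. Denominator: enumerated women who were under 19 at some time in the preceding 2 years, which means roughly ages 15 to 20 at the census. Numerator: those among them who had a pregnancy while under 19 in that period. Take the denominator from the household roster and the numerator from the maternity histories. A denominator of women aged 15 to 18 at the census would not do, because it misses those who were pregnant under 19 and have since turned 19 or 20. Keep the present share as a descriptive figure.

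Leave outcome 4 as defined and read it alongside outcome 2 (home deliveries).

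Cost: a change of definition, using information the census is already planned to collect. Age at pregnancy has to be derived from age at census and the timing of the pregnancy. Pregnancies in unmarried adolescents remain largely uncaptured, a limit the protocol already accepts by centering pregnancy outcomes on married women, so the rate counts captured pregnancies only. The result is slightly less comparable with sources that report shares, which is the reason to retain the share descriptively.
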